### Study conditions

#### The wait-list control group

Participants in the waiting list will not receive an intervention. They will complete assessments at all four time points. They could receive the intervention after the experimental group has completed all the assessments.

### Video-based transdiagnostic REBT prevention program

The authors, both being certified in REBT from Albert Ellis Institute, New-York, have developed a transdiagnostic REBT protocol for this study by adjusting existent protocols for internalizing problems in adolescents [43, 44]. Namely, our protocol was based on REBT theory [21]. Further, we shortened existent programs in order to investigate the efficacy of a briefer version of the protocol. The prevention program will be delivered in the school context, namely in adolescent’s school classes after regular school hours. The program will consist of six 50 min sessions of video-based REBT (See Table 1 for a content of each session) delivered for three weeks (two times per week) in a group format. Research assistants (Masters students, psychologists trained in CBT) will present each session based on a video cartoon and after this, a standardized PowerPoint presentation will be used to guide the discussion with the adolescents. They will learn various aspects related to internalizing problems, how irrational beliefs influence dysfunctional emotions, how to construct a hierarchy of feared situations and how to expose gradually. Also, they will learn breathing and relaxation exercises. Between sessions, homework will be provided and will be checked at the beginning of each session. The content of each session is presented as follows:

**Table 1 Tab1:** Protocol contents for each session

Session number	Content
1	Psychoeducation regarding internalizing problems
2	How to identify anxiety and depression. Relaxation
3	The ABC model of distress
4	Cognitive restructuring
5	Exposure and behavioral activation. Problem solving
6	Maintenance of therapeutic gains and relapse prevention

Session 1. *Psychoeducation regarding internalizing problems*. In this session, adolescents will be provided with information regarding internalizing problems. Videos regarding different internalizing symptoms will be presented and discussions regarding different types of symptoms will be initiated with the adolescents. Also, they will be informed about the program and about their involvement in this program.

Session 2. *Anxious and depressive symptoms identification and relaxation exercises*. In this session, adolescents will learn how to recognize anxiety and depression. Also, they will learn the four levels on which such emotions appear: physiological, subjective, cognitive, and behavioral. They will learn the importance of relaxation exercises in order to decrease physiological arousal and they will practice in class a relaxation exercise.

Session 3. *The ABC model of distress*. In this session, adolescents will be thought the ABC model of distress, where A stands for activating events, B stands for beliefs and C stands for consequences. They will learn to distinguish between rational and irrational beliefs, functional and dysfunctional emotions, and discover how different irrational beliefs (e.g., demandingness, awfulizing/catastrophizing, low frustration tolerance, global evaluation of human worth) are related to different negative dysfunctional emotions (e.g., anxiety, depression) according to the REBT theory. Finally, they will practice examples in which different activating situations are related to different emotions through the influence of irrational beliefs.

Session 4. *Cognitive restructuring*. In this session, adolescents will identify, learn how to dispute their irrational beliefs logically (e.g., “Is your belief logical?”), empirically (e.g., “Is there any evidence sustaining your belief?”) and pragmatically (e.g., “Is this belief helpful in any way for you?”). Finally, participants will learn how to dispute their irrational beliefs (demandingness, catastrophizing/ awfulizing, low frustration tolerance and global evaluation of human worth) and to replace them with rational beliefs (preference beliefs, non-catastrophizing, high frustration tolerance, unconditional acceptance) associated with functional emotions and adaptive behaviors. Namely, in this session, the ABC model is integrated with other two important components, namely Disputation (D) and Effective new responses (E) (e.g., functional emotions and adaptive behaviors associated with the new beliefs), thus turning into the extended ABCDE model.

Session 5. *Exposure, behavioral activation and problem-solving*. In this session, adolescents will learn how avoidance perpetuates anxiety, and the difference between exposure and avoidance. They will build an exposure hierarchy comprised of fear ladders, with a gradual increase of the distress after disputing their irrational beliefs (e.g., irrational beliefs about the confrontation with feared stimuli). The will learn the role of behavioral activation in decreasing depressive mood and will be encouraged to do enjoyable things in order to decrease their depressive symptoms. The second part of this session, adolescents will learn the difference between emotional and practical problems. In this sense, they will learn how to solve practical problems by applying a problem-solving protocol.

Session 6. *Maintenance of therapeutic gains and relapse prevention*. Adolescents will learn how to set realistic expectations regarding the occurrence of internalizing symptoms, and instead of thinking that they will never feel anxiety or depression they will learn that negative emotions can occur, however by identifying and restructuring their irrational beliefs, they will be able to turn those negative dysfunctional emotions into negative functional emotions (e.g., worry, sadness). Finally, the last session will be a booster session, in which a summary of the program will be presented in order to review all the strategies that adolescents acquired throughout the prevention program so as to prepare them to handle future challenges.

Homework assignments will be given after each session and participants will have to monitor their emotions (e.g., functional and dysfunctional emotions), their thinking patterns (e.g., identify the ABC components from personal examples), dispute their irrational beliefs and replace them with rational beliefs (e.g., the expanded ABCDE model), practice relaxation exercises (e.g., deep breathing, progressive muscle relaxation) at home and in other settings, practice exposure in imaginary and in vivo (e.g., behavioral assessments such as shame-attacking exercises), practice behavioral activation.

#### Therapists

Therapists (*N* = 5) will be Masters Students, psychologists trained in CBT, under supervision. Therapists will be trained before conducting the sessions with the adolescents and weekly supervision sessions will be conducted with the team.

### Data collection

Adolescents will complete all the assessments at school, in their classrooms, in the presence of a research assistant, blind to group allocation, that will provide assistance if needed. All the instruments will be applied in a paper and pencil format. Adolescents will complete assessments at four time-points: T_1_ (baseline), T_2_ (post-intervention), T_3_ (3 months follow-up) and T_4_ (12 months follow-up). An overview of the instruments that will be used for baseline, post-treatment, 3 months follow-up and 12 months follow-up is provided in Fig. 2.

**Fig. 2 Fig2:**
[figure not shown]
Overview of enrollment, intervention and assessment measures. *t_1x_, t_2x_ and *t_3x_ represent the program duration (3 weeks). Note. T1 = Baseline/pre-intervention, T2 = post-intervention, T3 = 3 months follow-up, T4 = 12 months follow-up

### Outcomes

#### Demographic data

Both adolescents and their parents will complete a questionnaire regarding their demographic characteristics, such as gender, age, urban or rural residency and completed years of education.

### Primary outcomes

#### Anxiety symptoms

The Multidimensional Anxiety Scale for Children (MASC) [45] will be used to assess anxiety symptoms in adolescents. This instrument consists of 39 items, rated on a four-point Likert scale, where 0 means *Never true* and 3 means *Often true*. This scale has four subscales, namely: Physical Symptoms, Social Anxiety, Harm Avoidance and Separation Anxiety/Panic.

#### Depressive symptoms

The depression subscale of the *Beck Youth Inventories™ -Second Edition for Children and Adolescents (BYI-II)* [41] will be used to assess adolescents’ depressive symptoms. BYI-II can be used with children and adolescents with ages between 7 and 18 years. This subscale contains 20 items, rated on a 4 point Likert scale, with 0 = *Never* and 3 = *Always*. The total score is obtained by summing the 20 items.

### Secondary outcomes

#### Comorbid problems

The Strengths and Difficulties Questionnaire (SDQ) [46] self-reported version for youths aged 11–17 will be used in this study. SDQ consists of 25-items, rated on a three-point Likert scale, where 0 means *Not true* and 2 means *Certainly true*. This instrument has five scales: Emotional problems, Conduct problems, Hyperactivity, Peer problems, and Prosocial behavior. This scale allows to compute a Total difficulties score, by summing the first three previously mentioned scales; also, two total scores for Internalizing (by adding emotional and peer problems scales) and Externalizing (by adding conduct and hyperactivity scales) can be computed [47]. We will use the Externalizing problems scale in order to investigate whether the program will have a significant impact on comorbid problems that adolescents may present. Also, we will use the Prosocial behavior subscale in order to investigate potential significant changes in positive outcomes.

#### Maladaptive cognitions

The Children’s Automatic Thoughts Scale – Negative/Positive (CATS-N/P) [48] will be used to assess negative and positive automatic thoughts in adolescents. CATS-N/P consists of 50 items, rated on a 5 point Likert scale, where 0 means *Not at all* and 4 means *All the time*. Total negative automatic thoughts score is computed by summing the three subscales, namely: Physical Threat, Social Threat, and Personal Failure, consisting of 40 items, while total positive automatic thoughts scale consists of 10 items. This instrument showed adequate psychometric properties (e.g., internal consistency, discriminant validity) previously [48].

#### Quality of life

The Questionnaire for Measuring Health-Related Quality of Life in Children and Adolescents, The Revised Version – adolescent version (Kiddo-KINDL) [49] will be used to assess adolescents’ quality of life. KINDL-R-a consists of 24 items that can be used with children and adolescents aged 3–17 years old. It has six subscales with four items each (physical and emotional well-being, self-esteem, family, friends, and school), all items scored on a 5-point scale.

#### Treatment expectancies

We translated and adapted The Credibility/ Expectancy Questionnaire [50] in order to use this instrument to assess adolescent’s expectancies regarding the prevention program. This instrument consists of six items, four of them scored on a 9 point Likert scale (1 = *Not at all*, 9 = *Very much*) while for two items participants will have to choose a percentage between 0% and 100% for expected improvement in their problems.

#### Satisfaction with the intervention

The Romanian version of the Client Satisfaction Scale, that has been previously used to assess satisfaction with an Internet-delivered CBT [51], will be used in order to assess participants’ satisfaction with the intervention. This scale consists of 10 items rated on a 5 point Likert scale (1 = *Don’t agree at all* and 5 = *Very much agree*). Higher scores on the Satisfaction with treatment scale will indicate greater levels of satisfaction with the program.

### Statistical methods

Statistical analyses were conducted using SPSS 23.0 software. First, independent t-tests and Chi-Square tests will be conducted in order to explore potential differences between participants from the two groups regarding age, gender, anxiety, depressive symptoms, irrationality, comorbid conditions, and quality of life. At post-treatment (T2), three months follow-up (T3) and twelve months follow-up (T4), continuous analysis will be conducted using intent-to-treat (ITT) principle the last observation carried forward. In order to assess the efficacy of the video-based transdiagnostic REBT universal prevention program to reduce anxiety and depressive outcomes as compared with the control group over time, we will use mixed effects models (random intercept and slope for time, a fixed effect for group). For effect size data we will use Cohen’s *d* (small effect size *d* = .20, medium effect size *d* = .50, large effect size *d* = .80; [52]). Mediation and moderation analyses will be conducted using PROCESS macro [53].

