### Design

A two-arm cluster randomized controlled trial (RCT) will be conducted. Participants’ school classes will be randomized by a computer software (www.randomizer.org) in one of the two treatment conditions: (1) video-based transdiagnostic REBT universal prevention program or (2) waitlist control. Assessments will be conducted at four time points: baseline (T_1_), post-intervention (T_2_), 3 months follow-up (T_3_) and 12 months follow-up (T_4_). Figure 1 illustrates the flowchart of the study.

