### Randomization and blinding

Randomization will be applied within classes, using a random numbers generator (www.randomizer.org), with an equal number of experimental and control groups within one school. Children will be assigned to either video-based transdiagnostic REBT universal prevention or to waitlist control condition. Allocation concealment will be done by an independent researcher, using opaque, sealed envelops that will be opened sequentially. Blinding of participants, researchers and assessors will be maintained.

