### Sample size calculation

A priori power analyses using G*Power version 3.1.5 [42] indicated that a total sample size of 260 would be sufficient to detect a small to medium effect size (*d =* .35) according to the results or previous research, for a two-tails between-group comparison at posttest, with an alpha of .05 and a power of 80%. As we expected to have a 30% dropout rate, we will recruit 169 participants in each group.

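### Baseline differences are to be tested with pupil-level t-tests and chi-square tests although classes are randomised, so the p-values will be wrong by an amount the document does not fix; a minor point with a nearly free remedy.

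*Protocol article*

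**What the plan says.** The first analysis step in Statistical methods is that "independent t-tests and Chi-Square tests will be conducted in order to explore potential differences" between participants of the two groups "regarding age, gender, anxiety, depressive symptoms, irrationality, comorbid conditions, and quality of life". No class term or other allowance for clustering is mentioned for these tests, and no significance level is given for them.

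The title calls the study a cluster randomised trial, and Design says that "school classes will be randomized by a computer software". Randomization and blinding is less clear. It says "Randomization will be applied within classes, using a random numbers generator" and then speaks of children being assigned, but it also requires allocation "with an equal number of experimental and control groups within one school", which only makes sense if whole groups are allocated.

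The efficacy model in Statistical methods has random intercepts and time slopes and a fixed group term. It names no class effect and no baseline covariates. Demographic data are collected, "such as gender, age, urban or rural residency and completed years of education", and the outcome scales are completed at T1.

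**The concern.** A two-sample t-test or chi-square test on pupils takes its standard error from the number of pupils. If classes are the units allocated, chance differences between arms vary more than that standard error allows, because pupils in a class share a grade, teachers and a social setting. A perfectly sound randomisation can then produce too many small p-values.

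Even a valid test of this kind says little. If pupils enter the trial without regard to allocation, any baseline difference is due to chance by construction. Seven independent valid 5% tests would still flag at least one difference in 30% of trials.

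At stake is how the baseline table is read. A spurious significant difference casts doubt on the randomisation and tempts the analyst to pick covariates after seeing the data.

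**Working it through.** **Inputs from the document.** The tests are at pupil level and cover seven variables (Statistical methods). The unit of allocation is the school class (title, Design). Arms are balanced within school (Randomization and blinding). The sample size section works two-sided, "for a two-tails between-group comparison at posttest", "with an alpha of .05 and a power of 80"%; the same 5% two-sided level is assumed here for the baseline tests.

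**Inputs not in the document, assumed.** Class size m is taken as 10 to 25 pupils, the ICC between classes as .01 to .05 for symptom scores, and the number of classes in the simulations as 12 to 16.

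**The plan's own figure.** None is given for the baseline tests. The nearest is the total of 260 for d = .35. The normal approximation gives 129 per arm, and the exact t-test gives 80.27% power at 130 per arm, so 260 reproduces. It reproduces as a calculation on independent pupils, with no allowance for class.

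**Symptom scores.** With design effect DE = 1 + (m − 1) × ICC, the true rejection rate of a nominal 5% test is 2 × [1 − Φ(1.96/√DE)].

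| m | ICC .01 | ICC .02 | ICC .05 |
|---|---|---|---|
| 10 | DE 1.09, 6.0% | DE 1.18, 7.1% | DE 1.45, 10.4% |
| 20 | DE 1.19, 7.2% | DE 1.38, 9.5% | DE 1.95, 16.0% |
| 25 | DE 1.24, 7.8% | DE 1.48, 10.7% | DE 2.20, 18.6% |

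Simulation with 12 to 16 classes of 21 to 28 pupils agrees: about 9% to 11% at a class ICC of .02 and 16% to 21% at .05. If the same total of .02 is split as .01 between schools and .01 between classes, the rate falls to about 7% to 8%, because balance within school removes the school part from the arm difference. The rate reaches 15% only at an ICC of about .045 (m = 20) or .036 (m = 25).

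**Age.** Assume grade-based classes, with equal numbers per arm in each school.
- Grades free to differ between arms: 41% rejections with 7 schools of 2 classes, 37% with 4 of 4, 46% with 3 of 4 (4,000 runs each). A variance-component version with ICC .3 between schools and .5 between classes gives 57% to 64%.
- Same-grade classes paired within school: 0.0% in all three layouts. The test is then conservative.

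The document does not say which of these applies.

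**Seven tests.** If all were valid and independent, 1 − .95⁷ = 30%.

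**Value of adjusting for T1.** Assume a T1–T2 correlation of .6 and unit variance. A post-test-only contrast has variance 1. Change from T1 has 2 × (1 − .6) = .80. Covariate adjustment leaves 1 − .6² = .64. The reduction is 36% against post-test only and 1 − .64/.80 = 20% against change from T1. It is smaller still if the mixed model already uses T1 efficiently as a repeated response.

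**The case against.** The strongest reply is that these tests are exploratory and change nothing. That largely stands: the text only says that differences will be explored, and it attaches no decision on comparability, covariates or model form. A reader might infer that comparability will be judged by these p-values, or that they are the plan's only handling of baseline differences. The document supports neither. The efficacy model assesses change over time, and T1 may already enter it as a repeated measure.

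A reader might also infer false alarms several times the nominal rate, and worst of all for age. With class size and ICC unstated, small classes and low ICCs give only 1.2 to 1.9 times nominal (6.0% to 9.5% at 10 to 20 pupils and ICC .01 to .02), and pairing by grade would make the age test conservative. Nor can the symptom-score rates be compounded over the seven variables as if independent: anxiety, depression, cognitions and quality of life are correlated.

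Two further points carry weight. If children were allocated individually, as one sentence of Randomization and blinding can be read, the rate would be 5%; the title, the Design section and the balance of groups within schools speak against that reading. And in a cluster trial a baseline check is not pointless if pupils could be recruited after allocation is known: consent is placed before assessment, not expressly before randomisation. Such a check would still have to allow for class.

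Finally, a covariate list may properly sit in an analysis plan not shown here, so its absence from the article is not a fault. What remains is a stated method that does not fit the stated design.

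**Conclusion.** The point holds as a minor one. The article fixes pupil-level tests for baseline differences in a trial that randomises classes, and their p-values are wrong whenever pupils cluster by class. For symptom scores the illustrative rejection rate is about 6% to 19% instead of 5%, under assumed class sizes of 10 to 25 and ICCs of .01 to .05, and lower where clustering lies between schools. For age the direction itself is open, from near 0% to over 40%, because the handling of grade within school is not stated.

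The efficacy estimate is untouched. The absence of class from the sample size and from the efficacy model as described is a separate and weightier matter; correcting it would not correct this sentence.

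**What to change.** Replace the sentence on baseline tests. Report T1 means, SDs and percentages by arm, with the numbers of classes and pupils and without p-values. If a check for differential recruitment is wanted, use a method that allows for class.

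Prespecify age and gender as covariates in the efficacy model, whatever imbalance is seen, together with a class random effect. Adjust for the T1 score of the outcome in one way only: either as a covariate with T2 to T4 as responses, or as a repeated response with a common baseline mean for the two arms. Doing both would use T1 twice.

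The cost is one replaced sentence and a slightly longer model statement; every variable needed is already collected. The gain in precision depends on the T1–T2 correlation and on how the present model already uses T1, so no single figure should be promised for it.

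### School classes are randomised, but the stated efficacy model has no class term or other allowance for clustering, so the standard error of the group effect is too small for any positive intraclass correlation

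*Protocol article*

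**What the plan says.** The title and the Design section call this a cluster trial: "A two-arm cluster randomized controlled trial (RCT) will be conducted". Design also names the unit: "school classes will be randomized by a computer software (www.randomizer.org) in one of the two treatment conditions". The section on the prevention program places the sessions in the pupils' school classes, "delivered for three weeks (two times per week) in a group format".

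Randomization and blinding is less clear. It opens with "Randomization will be applied within classes, using a random numbers generator" and later speaks of children being assigned. The same opening sentence, however, ends with "with an equal number of experimental and control groups within one school", which describes classes allocated in equal numbers within each school.

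Statistical methods gives the efficacy model in one parenthesis: "we will use mixed effects models (random intercept and slope for time, a fixed effect for group". It does not mention class or school. The baseline t-tests and chi-square tests and the PROCESS mediation and moderation analyses also come without any allowance for clustering. Sample size calculation gives 260 participants for d = 0.35, two-sided alpha 0.05 and 80% power, with no ICC, class size or design effect.

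**The concern.** Pupils in one class share their allocation and, in the experimental arm, their sessions and the person who leads them. Their outcomes are therefore likely to be correlated, and the arms differ partly by which classes fell into each. A model whose random effects sit only at the participant level leaves this between-class variance out of the standard error of the group effect. Confidence intervals are then too narrow and p-values too small, for both the anxiety and the depression primary outcomes. A significant result could not be taken at its nominal level.

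The article does not simply leave the model for later. It lists the random and fixed effects, and the randomised unit is not among them.

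**Working it through.** **1. The plan's own sample size.** Inputs from Sample size calculation: d = 0.35, two-sided alpha 0.05, power 80%. The normal approximation gives 129 per arm (258 in total). The noncentral t calculation gives 130 per arm, 260 in total, with power 80.3%. The stated 260 is thus exactly the figure for independent pupils, so the design stage makes no allowance for clustering either.

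**2. Error of a group test that ignores class.** The documents give no class size m and no ICC, so both are assumed. With design effect DE = 1 + (m − 1) × ICC, the true two-sided error of a nominal 5% test is 2 × [1 − Φ(1.96/√DE)].

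| Participants per class | ICC 0.01 | ICC 0.02 | ICC 0.05 |
|---|---|---|---|
| 10 | DE 1.09, 6.0% | DE 1.18, 7.1% | DE 1.45, 10.4% |
| 20 | DE 1.19, 7.2% | DE 1.38, 9.5% | DE 1.95, 16.0% |
| 25 | DE 1.24, 7.8% | DE 1.48, 10.7% | DE 2.20, 18.6% |

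**3. The stated model.** This was simulated with a participant random intercept and slope, known variances and class omitted. There were 6 classes of 20 per arm, four equally spaced times and 20,000 runs. The assumed variances were 0.60 for the intercept (class share included), 0.03 for the slope and 0.35 for the residual. The group effect was rejected in 5.0% of runs with no class variance, 10.7% with class variance 0.02 and 19.4% with 0.05. These rates exceed the m = 20 row because combining four measurements removes residual noise but not the class component.

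**4. A group-by-time test.** In the same simulation, the error was 4.9% and 4.8% when class differences (variance 0.02 and 0.05) were constant over time. It was 6.2%, 8.4% and 11.5% when classes held 2%, 5% and 10% of the slope variance.

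The formula in step 2 agrees. With times 0, 1, 2, 3, the sum of squares about the mean is 5, so a pupil's fitted slope has variance 0.03 + 0.35/5 = 0.10. Class shares of 2%, 5% and 10% of 0.03 are then ICCs of 0.006, 0.015 and 0.03 for the fitted slope. The design effects at m = 20 are 1.11, 1.29 and 1.57, and the errors about 6%, 8% and 12%.

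**5. School alone.** With a school ICC of 0.05, no class variance and arms balanced within school, a test without a school term rejected in 4.5% of simulated runs.

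**6. Power once class is modelled.** Take the plan's 260 as analysed (130 per arm) and 20 per class. Power is Φ(0.35/√(2 × DE/130) − 1.96). At ICC 0.02, DE = 1.38 gives Φ(2.40 − 1.96) = 0.67. At ICC 0.05, DE = 1.95 gives Φ(2.02 − 1.96) = 0.52. These figures are before any loss from few degrees of freedom: 338 pupils in classes of 20 to 25 make only about 14 to 17 classes (338/25 = 13.5; 338/20 = 16.9).

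**The case against.** The strongest reply is that this is a condensed article, that the model fills one parenthesis, and that the level of the random intercept is not named. A full specification might include class. This stands in part: a reader should not take it as settled that the final analysis will treat classmates as independent. But with a random slope for time the random effects read naturally as the participant's, no clustering allowance appears anywhere, and the sample size is the one for independent pupils. Adding class later would change the published model, not elaborate it.

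A reader might also infer that the error is well above 5%. The documents do not support that as a general statement, because they give no ICC or class size. Nor do they say that whole classes take part: parental consent and adolescent assent are required and sessions follow school hours, so participating groups may be small. With 10 per class and ICC 0.01 the error is 6.0%.

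The stated purpose is a comparison with control over time, so the intended test may be group-by-time, where stable class differences cancel. This is a fair point and it lowers the figures. However, the only fixed effect named is group, where the inflation is full, and group delivery makes differing class trajectories plausible.

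Finally, a reader might blame the missing school term equally. Arms are balanced within school, and omitting school alone did not raise the error.

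**Conclusion.** The defect holds as written: the class is randomised and the stated efficacy model does not contain it. The direction is certain for the group effect at any positive class ICC. The size rests on assumed values: about 6-10% true error with 10 per class and about 7-19% with 20 to 25 per class, over ICC 0.01 to 0.05. For group-by-time it is about 5% if class differences are constant and about 6-12% if classes hold 2-10% of the slope variance, under the variance components in step 4. The missing class term is the cause, not the missing school term.

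The opening words of Randomization and blinding could suggest that pupils are randomised individually inside a class. The title, the Design section and the rest of that same sentence point to classes randomised within schools. The wording still needs reconciling, because it determines which analysis is valid.

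**What to change.** - In Statistical methods, state a model with repeated measures within adolescent within class and a random class intercept. Say whether group or group-by-time is the efficacy test; if it is group-by-time, add a class-by-time random term, since a class intercept alone does not protect that contrast when class trajectories differ.
- Include school as a fixed stratum, because allocation is balanced within it, and name a small-sample degrees-of-freedom method such as Satterthwaite, because there will be few classes.
- Apply the class term to the secondary outcomes, and say how the mediation and moderation analyses allow for class.
- Reword Randomization and blinding to agree with Design: classes are randomised within schools.
- In Sample size calculation, state that 80% power assumes no clustering, and give power over a range of ICC and class size.

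No new data are needed, since randomisation itself requires class and school to be known, and the article reports recruitment as ongoing, so the change can still be pre-specified. The costs are wider confidence intervals and a lower admitted power, as in step 6.
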